### **9.6.2. Description of comparator**

Participants will follow the local standard care pathway that may include advice and support on pre-rehabilitation.

### **9.6.3. Cancer waiting times**

NHS Cancer Waiting Times Monitoring Dataset Guidance gives strict requirements for time to first definitive treatment date for curative colorectal surgery. As per the latest guidance and another national pre-habilitation trial in the field, the date of consent given by a participant to be entered into the trial will be the first definitive treatment date for this purpose in line with the above guidance [63, 64]. The pre-operative intervention part of this study has been designed to fit within the targets of cancer waiting times guidance. Surgery should not be unduly delayed as a result of entry into the study.

### **9.6.4. Description of study procedure(s)**

#### Demographic questionnaire – 2 mins

Basic demographic characteristics including date of birth, sex, and ethnicity will be captured using standardised questions. Contact details (home address, contact number(s), GP practice address, next of kin) will be extracted from medical records and verified by the patient.

#### EuroQoL-5D 5-level version (EQ-5D-5L) questionnaire – 5 mins

Widely used and validated general HRQoL instrument assessing mobility, self-care, usual activities, pain/discomfort and anxiety/depression as well as overall self-rated health.

#### European Organisation for Research and Treatment of Cancer Quality of Life Questionnaire – Colorectal cancer module (EORTC-QLQ-CR29) – 10 mins

Widely used and validated CRC-specific HRQoL instrument assessing CRC-specific functional status and symptoms post-operatively.

Hospital Anxiety and Depression Scale (HADS) – 5 mins

Widely used and validated anxiety and depression questionnaire.

Resource use questionnaire – 5 mins

A modified Client Service Receipt Inventory [65] will be used to collect data on use of primary care services, social care services, and other health care professional, as well as time off work.

Concomitant medication (5 min)

Participants will be asked to bring their prescription or a list of their medication at the screening visit for these to be recorded.

Weight and body composition – 3 mins

Weight will be measured barefoot and with light clothing to the nearest 0.1kg using a calibrated digital scale which will also estimate body composition using bioelectrical impedance.

Height – 2 mins

Height without shoes will be measured to the nearest 0.1cm using a stadiometer.

5 times sit to stand test – 3 mins

Participants sit in a standard straight-backed stable chair (without wheels) positioned by a wall. They then stand fully and sit back down, without using the hands, five times, as quickly as possible.

Post-operative complications

Presence and type of any morbidity. This will be based on medical records for complications during the hospital stay and on participants reporting it using a standard proforma for complications following discharge. They will be graded (as I-V) independently by two researchers blinded to treatment allocation with the Clavien-Dindo classification of post-operative complications, the most widely used and validated measure.[66]

Table 1: Clavien-Dindo classification of post-operative complications

| Morbidity grade definition |                                                                                                                                                                                                                                                                                                                                                             |
|----------------------------|-------------------------------------------------------------------------------------------------------------------------------------------------------------------------------------------------------------------------------------------------------------------------------------------------------------------------------------------------------------|
| I                          | Any deviation from the normal postoperative course without the need for pharmacological treatment or surgical, endoscopic, and radiological interventions.
Allowed therapeutic regimens are: drugs as antiemetics, antipyretics, analgesics, diuretics, electrolytes, and physiotherapy.
Grade I also includes wound infection opened at the bedside. |
| II                         | Requiring pharmacological treatment with drugs other than those allowed for grade I complications.
Grade II also includes blood transfusions and total parenteral nutrition.                                                                                                                                                                             |

---

|      |                                                                                                                         |
|------|-------------------------------------------------------------------------------------------------------------------------|
| III  | Requiring surgical, endoscopic, or radiological intervention.                                                           |
| IIIa | - Not under general anaesthesia                                                                                         |
| IIIb | - Under general anaesthesia                                                                                             |
| IV   | Life-threatening complication (including central nervous system complications) requiring intensive care unit management |
| IVa  | - Single organ dysfunction                                                                                              |
| IVb  | - Multiorgan dysfunction                                                                                                |
| V    | Death                                                                                                                   |

---

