### **9.5. Blinding and code-breaking**

It is impossible to blind the participants and research nurses due to the nature of the intervention. Therefore, procedures for breaking the allocation code are not applicable. However, the assessors of the future primary outcome (research nurses conducting the post-operative follow-up visit) will be blinded.

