#### Operative outcomes

These will be extracted from medical records.

At discharge:

- *Intraoperative blood loss, in mL*
- *Operative time, in minutes*
- *Conversion to open surgery (yes/no)*

At discharge and 30 days post-operatively:

- *Surgical site infection*
- *Rate of stomas and stoma-specific complications*
- *Presence of radiologically-defined anastomotic leaks*
- *Time in intensive care unit and high dependency unit*

At 30 days post-operatively and at 3 years:

- *Re-operation rate*
- *Re-admission rate*

Descriptive data on the initial operation approach, operation type, and grade of surgeon performing the operation, will also be extracted.

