## 2. BACKGROUND AND OBJECTIVES

### 2.1 Brief synopsis

This trial is a study of a pre-operative intentional weight loss intervention intended to support post-operative recovery in patients with overweight and colorectal cancer, aka “the CARE feasibility parallel randomised controlled trial”. It is intended to examine the feasibility of progression to a definitive randomised controlled trial that will examine whether a supported weight loss intervention aimed at overweight adults awaiting colorectal cancer surgery can reduce complications.

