## 6. MORBIDITY

### Morbidity

| #  | Outcome Measures                                             | Control | Intervention | Delta |
|----|--------------------------------------------------------------|---------|--------------|-------|
| 2a | i. Any morbidity                                             |         |              |       |
|    | At or prior to discharge                                     | X       | X            | X     |
|    | Between discharge and 30 days                                | X       | X            | X     |
|    | Other                                                        | X       | X            | X     |
|    | Total                                                        | X       | X            | X     |
|    | At or prior to discharge
OR between discharge and 30 days | X       | X            | X     |
| 2b | ii. Morbidity by grade (I, II, IIIa, IIIb, IVa, IVb)         |         |              |       |
|    | at least one Grade I                                         | X       | X            | X     |
|    | .                                                            | X       | X            | X     |
|    | at least one Grade IVb                                       | X       | X            | X     |
|    | Other                                                        | X       | X            | X     |
|    | Total                                                        | X       | X            | X     |
| 2c | iii. Survival (grade V)                                      | X       | X            | X     |
| 2d | iv Morbidity by highest grade                                | X       | X            | X     |
| 2e | v. Number of people with no morbidity                        | X       | X            | X     |
| 2f | vi. Morbidity by type (eg arrhythmia, wound infection, etc)  |         |              |       |
|    | Type                                                         | X       | X            | X     |
|    | .                                                            | X       | X            | X     |
|    | Type                                                         | X       | X            | X     |
|    | Other                                                        | X       | X            | X     |
|    | Total                                                        | X       | X            | X     |

Note: the "other" categories are included for completeness and will be omitted if absent

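### Complications after discharge rest on the unblinded participant's own report, although hospital records are already extracted to day 30 for other outcomes

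*Combined protocol and SAP*

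**What the plan says.** Protocol 9.6.4 (Post-operative complications) takes the presence and type of morbidity from "medical records for complications during the hospital stay and on participants reporting it using a standard proforma for complications following discharge". The events are then "graded (as I-V) independently by two researchers blinded to treatment allocation", using the Clavien-Dindo scale. Protocol 9.5 states that "It is impossible to blind the participants and research nurses due to the nature of the intervention", but also that "the assessors of the future primary outcome (research nurses conducting the post-operative follow-up visit) will be blinded". Protocol 9.8 places complications reporting at the face-to-face visit around day 30.

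For the operative outcomes, the same section 9.6.4 says "These will be extracted from medical records". At 30 days these include surgical site infection, stoma complications, radiological leaks, intensive-care and high-dependency time, re-operation and re-admission. Survival at 30 days is also taken from records. Protocol 11.11 expects the recruiting hospital to provide all of a patient's secondary care.

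The SAP supplement on secondary outcomes derives morbidity from two forms, Complications Grading 1 and 2 (sections 6.1, 6.2, 6.4 and 6.6). Its section 6 table has rows for events up to discharge, for "Between discharge and 30 days", and for either period. It names no source for any row and describes no check of the proforma against records.

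**The concern.** The source of the outcome changes at discharge, from a hospital record to the account of someone who knows their arm. Blinding the graders protects their judgement but not the material they judge. A complication that the participant does not mention never reaches them, and neither does a drug treatment described too vaguely to separate grade I from grade II. A better source for hospital-managed events is already opened at day 30 for other outcomes, yet the plan does not connect it to the grading.

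SAP 2.1 says the definitive trial is to examine "whether a supported weight loss intervention aimed at overweight adults awaiting colorectal cancer surgery can reduce complications". This study is therefore where the measurement of complications is rehearsed, and a weak source rule could be carried into the larger trial.

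**Working it through.** The plan states no figure on this point, so there is none to reproduce. The check sets the sections side by side and then adds simple arithmetic.

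**1. Sources after discharge**
- Clavien-Dindo morbidity: participant proforma (protocol 9.6.4).
- Infection, leak, stoma complications, intensive-care and high-dependency time, re-operation, re-admission, survival: medical records at 30 days (protocol 9.6.4).
- Infection and leak in the supplement (8.4, 8.6): the Complications Grading 1 form, itself derived from earlier forms such as Hospital Stay and Discharge. Morbidity uses both grading forms. The documents do not say which period each form covers.

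No section says that the 30-day record data go to the graders, or which source prevails if the two disagree.

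**2. What grading needs**

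Protocol Table 1 grades by treatment received. Grade II turns on which drugs were given. Grade IIIa is "Not under general anaesthesia", against IIIb under it. Grade IV turns on intensive-care management and the number of failing organs. Many grade III to V events leave a trace in the record-based outcomes listed above. Grade I and II events after discharge often would not, so the gap is mainly there.

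**3. Withdrawn participants**
- Protocol 9.10: the default withdrawal option ends active follow-up but keeps record access.
- Protocol 11.4 and supplement 3: those who had surgery stay in the main analysis regardless of withdrawal.
- Supplement 6.1: the rate is patients with at least one complication divided by the number of patients.
- Supplement 15.1: missing data are not imputed. It points to the sensitivity analyses, but 15.4 lists none for missing morbidity.

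Read together, such a participant completes no proforma and can count as event-free after discharge while their records remain available.

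**4. Calendar time under the proforma rule**

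Share = (end of window − discharge day) / end of window. Appendix B gives discharge at about day 5 to 7.
- Nominal day 30: (30 − 7)/30 = 23/30 = 77%, to (30 − 5)/30 = 25/30 = 83%.
- Allowed visit window, day 27 to 37 (protocol 9.8): (27 − 7)/27 = 74%, to (37 − 5)/37 = 86%.

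The documents do not give the timing of complications, so these are not shares of events.

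**5. Illustration of size, under assumptions**

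Spurious difference = M × s × d, with the same true morbidity M in both arms. M = 43% is the figure for patients with obesity in protocol section 5. Assumed: s, the share of affected participants whose only events come after discharge, is 20% to 50%; d, the between-arm difference in reporting sensitivity, is 10 to 30 percentage points.
- Low: 43 × 0.20 × 0.10 = 0.9 points.
- High: 43 × 0.50 × 0.30 = 6.5 points.
- Equal reporting (d = 0): 0 points.

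For loss to follow-up, take 72 as the retention denominator (assumed). The green threshold of 85% requires 0.85 × 72 = 61.2, so 62 retained, and up to 10 of 72 (13.9%) may be lost. If all 10 had surgery and none of their post-discharge events were captured, the pooled any-morbidity rate would be too low by (10/72) × 43 × 0.20 = 1.2 points to (10/72) × 43 × 0.50 = 3.0 points.

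**The case against.** The plan has real safeguards: a standard proforma, a face-to-face visit with a blinded nurse, and two blinded graders working independently. The procedure is the same in both arms, so a spurious difference needs unequal reporting, follow-up or timing of discharge. The supplement links infection and leak to one of the forms that feeds morbidity, and it already reports any morbidity and morbidity by grade regardless of timepoint, so the discharge split is only a display. Protocol 13.2 allows sample verification against patient notes. Hospital records would also miss events treated only in primary care, which the proforma can catch.

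All of this stands, and it limits the point. A reader might infer that post-discharge events cannot be graded reliably, that self-report alone covers 77% to 83% of complications, or that a definite fraction of events is lost. The documents support none of these. They contain no data on the accuracy of self-report, the percentages are calendar time, and many severe events are also captured from records. A reader might also infer that this trial's control-arm rate will size the definitive trial; no section says so. Protocol 9.5 does not name the future primary outcome either. That it is complications is an inference from SAP 2.1 and 5.4.

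The safeguards do not close the gap. None supplies the graders with what the participant omitted, and optional sampling of notes is not a source rule.

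**Conclusion.** The point holds as a weakness in how morbidity is ascertained, and it is worth correcting. Protocol 9.6.4 prescribes the weaker source for hospital-managed events after discharge while the stronger one is already extracted at day 30. It also leaves participants who withdrew with record access without any post-discharge source.

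The effect on the between-arm comparison cannot be quantified from the documents. It is zero if reporting and follow-up are equal in both arms; the 0.9 to 6.5 points above rest wholly on the assumed inputs. Morbidity is a secondary outcome, its intervals are nominal and descriptive (protocol 11.7), and no progression criterion uses it, so the decision to proceed is not affected by this route. The conclusion assumes that the recruiting hospital's records do hold the secondary care, as protocol 11.11 expects.

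**What to change.** In protocol 9.6.4 and supplement 6.1, 6.2, 6.4 and 6.6:
- Base presence and grade of complications on hospital records from surgery to day 30 in both arms, using the extraction that already supplies the 30-day operative outcomes and survival. Include participants who withdrew but allow record access.
- Keep the proforma as a supplement for events managed outside hospital.
- Give both sources to the blinded graders, let the record prevail where it covers the event, and record the source for each event.
- Name the sources beside the discharge split in the supplement's section 6 table and label that split descriptive.
- Align the operative-outcomes text in protocol 9.6.4 with supplement 8.4 and 8.6, and state which period each Complications Grading form covers.

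The cost is a wording change in both documents and modest extra abstraction time, since the records are already opened at day 30. The remaining limitation is that events treated only in primary care still rest on self-report.

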#### Adverse events (AEs)

Patient will self-report potential adverse events through a pre-defined list of expected adverse events based on previous trials of this type of intervention as well as free-text for any additional adverse event.

#### Fitness to discharge

This will be extracted from medical records and be used to calculate the length of hospital stay and, together with survival, the days alive and out of hospital.

#### Operative outcomes

These will be extracted from medical records.

At discharge:

- *Intraoperative blood loss, in mL*
- *Operative time, in minutes*
- *Conversion to open surgery (yes/no)*

At discharge and 30 days post-operatively:

- *Surgical site infection*
- *Rate of stomas and stoma-specific complications*
- *Presence of radiologically-defined anastomotic leaks*
- *Time in intensive care unit and high dependency unit*

At 30 days post-operatively and at 3 years:

- *Re-operation rate*
- *Re-admission rate*

Descriptive data on the initial operation approach, operation type, and grade of surgeon performing the operation, will also be extracted.

#### Oncological outcomes

These will be extracted from medical records

At discharge:

- *Resection margins, in millimetres*

At discharge, 30 days post-operatively, and 3 years:

- *Survival*

At 3 years:

- *Recurrence*
- *New primary/secondary cancer*

Descriptive data on tumour histological staging and standardised data for the National Bowel Cancer Audit will also be extracted.

*Feedback questionnaire pre-surgery by intervention participants – 2 mins*

This 8-item questionnaire will assess intervention acceptability using adapted questions from the Theoretical Framework of Acceptability questionnaire.[67]

*Feedback questionnaire post-surgery – 5 mins*

This 11-item study-specific questionnaire will assess satisfaction with trial processes, potential contamination of the usual care group, and satisfaction with the intervention for the intervention participants.

*QuinteT qualitative interviews to evaluate and optimise recruitment – optional – ~20min*

To explore experience of being approached, factors influencing trial participation, understanding and acceptability of the presence of chance in random allocation, comparison of the two naturally different trial groups, and perceived acceptability, benefits, and risks from being randomised to each group. All participants who consent to the main trial will be invited for this optional phone interview regardless of whether they accept or reject their allocation (e.g., do not start the intervention). This interview should occur where possible within 4 days of providing informed consent for the trial. The topic guide (Appendix D) may be refined as the study progresses, as per best practice. Interviews will be conducted over the phone/MS Teams, will be audio-recorded, and transcribed verbatim. For details on the QuinteT process, see 9.6.1.

*Qualitative interviews with intervention participants – ~45min*

Interviews will invite views on (a) the delivery of the programme, (b) barriers to engagement, (c) barriers to adherence, (d) facilitators to adherence while providing flexibility to participants to discuss their views in their own way highlighting aspects of experience that were particularly important to them. They will also capture participants' views on changes in physical activity. The sample size should allow saturation to be reached.[68] Interviews will also cover gastrointestinal symptoms relevant to both CRC and the intervention (e.g., constipation). The topic guide (Appendix E) may be refined as the study progresses, as per best practice. Interviews will be conducted over the phone/MS Teams, will be audio-recorded, and transcribed verbatim.

*Qualitative interviews with research and clinical staff – ~45min*

These interviews will aim to explore understanding of trial rationale, design, equipoise, perceptions of the intervention, whether staff would (or not) discuss the trial based on criteria beyond the

inclusion/exclusion criteria, concerns, perception of patients' reactions to the trial, recruitment procedures, and relevance of results to their own practice. The topic guide (Appendix F) may be refined as the study progresses, as per best practice. Interviews will be conducted over the phone/MS Teams, will be audio-recorded, and transcribed verbatim.

#### Fidelity of delivery

A researcher not delivering the intervention will observe a random 10% subsample of the initial dietetic consultations and a 10% subsample of the subsequent dietetic consultations (i.e., join the phone/video call) as they occur and code them with pre-specified criteria to assess fidelity of delivery.

